## Abstract

**Background:**

American Indian men are disproportionately impacted by prostate cancer (PC) compared to White men and experience the worst PC outcomes of any racial or ethnic group. To address these disparities, it is important to better understand American Indian men’s preferences regarding PC screening.

**Objective:**

The objectives of this study are as follows: (1) conduct a literature review, followed by qualitative, culturally responsive formative research with American Indian men, (2) develop and field a discrete choice experiment (DCE) survey to elicit the preferences of American Indian men toward PC screening, and (3) identify feasible, culturally appropriate, preference-concordant screening strategies that are targeted for American Indian men.

**Methods:**

In this protocol, a scoping literature review to identify previous PC DCEs has been created. We will follow that review by conducting rigorous, theoretically grounded qualitative work to identify plausible DCE attributes and attribute levels among men from the Lumbee Tribe in North Carolina. We will pilot the DCE among Lumbee men to assess cultural responsiveness and comprehension of the choice context and choice tasks. Finally, the DCE methodology will be used to elicit the PC screening preferences among 100 Lumbee men between the ages of 40 and 69 years. Choice data will be analyzed using mixed logit models, and trade-offs will be described using marginal rates of substitution.

**Results:**

The study was funded in 2024. Formative qualitative research is still ongoing. DCE data collection is expected to start in April 2026 and end in June 2026.

**Conclusions:**

This will be the first study to use a culturally responsive approach to DCE development in an indigenous population. The findings of this study can be used to educate providers regarding culturally responsive PC screening and to inform the design of interventions to increase preference-concordant PC screening in American Indian men.

## Introduction

Approximately 10 million people in the United States, or about 3% of the entire population, identify as American Indian or Alaska Native [1]. According to the Centers for Disease Control and Prevention, among American Indian men, prostate cancer (PC) is the second leading cause of cancer-related deaths [2]. Prior research shows that American Indian men are more likely to have advanced distant stage PC at the time of diagnosis compared to non-Hispanic White men. American Indian men have higher PC mortality rates, despite the fact that there is no underlying genetic difference between the 2 racial and cultural identities [3,4]. In North Carolina, recent epidemiological research has found that American Indian men are 72% more likely to die because of PC than non-Hispanic White men [5].

PC is the second most diagnosed cancer among men in the United States and the second leading cause of cancer-related deaths in men [6]. Identifying PC at its earliest stage is associated with a nearly 100% 5-year survival rate [7]. The most common method to screen for PC is through prostate-specific antigen (PSA) testing. PC screening guidelines are heterogeneous and have caused significant controversy around when and whom to screen [8,9]. PSA screening, however, comes with a significant risk of false positives and overdiagnosis (identifying tumors that would not impact a man’s life). Therefore, current guidance from the US Preventive Services Task Force (USPSTF) advises health care providers to use shared decision-making (SDM), starting at the age of 55 years through the age of 69 years, and present the benefits and risks of PSA screening, including overdiagnosis and overtreatment [10]. This is notably different from the 2012 to 2018 USPSTF guidance, which recommended against using PSA-based screening for all men.

While PSA screening has largely fallen out of favor in primary care settings for men with average PC risk, the Prostate Cancer Foundation and the American Urological Association recommend providers to conduct a baseline PSA test for Black men aged between 40 and 45 years and proceed to obtain annual PSA testing if PSA level is at or above 2 ng/mL [11], in contrast to current USPSTF guidelines [12]. The USPSTF guidelines, which are based on the Prostate, Lung, and Colorectal study, do not differentiate between high-risk men and average-risk men, and Black men are not included in their results. So, there is a general misunderstanding about the true sensitivity or specificity of the PSA. Currently, American Indian men are not identified by any organization as a high-risk population for PC, despite experiencing significantly worse outcomes than other racial and ethnic identities.

PSA-based PC screening is considered a preference-sensitive decision because there are multiple medically acceptable options [13]. Preference-sensitive decisions require providers to share the options that patients may have, their risks and benefits, and use SDM to arrive at a decision. Since patient input is required and patients are supposed to share their preferences in these situations, role preferences during medical encounters play an outsized role in these preference-sensitive decisions [14]. However, few studies that investigate patient preferences routinely take into account patients’ role preferences during medical encounters [15].

Persistent disparities in PC mortality due to underscreening, disparities in accessing treatment among American Indian men, and PC diagnoses at later stages of the disease suggest that new approaches are needed to reduce PC mortality in this population. However, less information is known about PC screening preferences, especially in the American Indian population. To understand and address disparities in PC screening rates and outcomes, it is important to study American Indian men’s preferences regarding this important screening test. Discrete choice experiments (DCEs) are routinely used to elicit and quantify preferences for health care decisions, including screening options for cancers and treatments in various real-world scenarios [16,17]. This makes DCE an excellent option to study PC screening preferences.

This study describes our study protocol for a research study aimed at identifying PC screening strategies that align with the preferences of American Indian men and also identifying key tradeoffs. To the authors’ knowledge, this study would be the first to use a culturally responsive approach to develop and field DCE. DCEs offer a novel approach that evaluates how PC screening characteristics interact with individual characteristics and preferences for designing targeted PC screening strategies.

The aims of this protocol report are as follows:

Conduct a literature review, followed by qualitative, culturally responsive formative research with American Indian men to develop a comprehensive understanding of facilitators and barriers to PC-related communication, explore role preferences in PC-related SDM, and prioritize preference-relevant features of PC screening strategies;Develop and field a DCE survey to elicit the PC screening preferences of American Indian men and identify barriers to and facilitators of PC screening uptake; andIdentify feasible, culturally appropriate, preference-concordant screening strategies targeted for American Indian men.

## Methods

### DCE Overview

The DCE methodology is a rigorous, quantitative, and theoretically grounded approach to elicit preferences. This methodology is based on two theoretical foundations: (1) Lancaster’s consumer theory and (2) random utility theory [18]. The assumption behind Lancaster’s consumer theory is that a person will choose a certain good or service based on an analysis of all its intrinsic characteristics or attributes. The combination of attributes gives rise to utility or value. Random utility theory states that utility (value) is a latent variable that exists but cannot be directly observed. Instead, it is assumed that when an individual chooses a good or service, its utility, that is, the value derived from the combination of all of its attributes, matches or exceeds that of all other alternatives considered. DCEs have been used in numerous pharmacoeconomic, health policy, and consumer preference evaluations in the United States and internationally [19].

The process for developing DCE will follow the guidelines outlined by the International Society for Pharmacoeconomics and Outcomes Research Good Research Practices for Conjoint Analysis Task Force [20].

### Study Design, Participants, and Setting

The study will be conducted in phases, including a systematic literature review, rigorous, theoretically grounded qualitative work, and the design, fielding, and analysis of the DCE. Study participants comprise people of the Lumbee Tribe in southeastern North Carolina. The Lumbee Tribe comprises approximately 55,000 people, making the tribe the largest American Indian tribe in North Carolina and one of the largest tribes in the eastern United States [21]. The Lumbee Tribe has been recently recognized by the federal government but has not yet received federal resources for health care services. Robeson County, where the majority of Lumbee Tribe people live, has the highest prevalence rates of cancers in North Carolina. Previous research has shown that American Indian men statewide in North Carolina have PC incidence rates 72% higher than non-Hispanic White men [5].

### Phase 1: Literature Review

First, our team conducted a scoping literature review to identify previous DCEs in PC screening. The goal of the scoping review was to identify which attributes have been previously included in PC screening DCEs and how attributes were operationalized into levels. We searched for articles in PubMed, Embase, Web of Science, and Global Index Medicus databases. We used the Covidence online web application (Melbourne, Australia) to manage the data. Articles were included in our scoping review if: (1) men or males at birth were included, (2) the outcome used marginal rates of substitution (mRS), latent class analysis, multivariable logit regression, or relative attribute importance, or (3) the study used any of the following types of study designs: (a) conjoint analysis, (b) DCE, or (c) best-worst scale. Our initial search identified 1140 studies, of which 273 were duplicates. Interrater reliability in article selection was Cohen κ=0.88. One author (CG) extracted study findings. *Appendix A* in Multimedia Appendix 1 presents the search strategies that we used to identify the literature. *Appendix B* in Multimedia Appendix 1 presents the data extraction template. Since this was a scoping review, we did not evaluate the quality of the included articles. *Appendix C* in Multimedia Appendix 1 presents the PRISMA (Preferred Reporting Items for Systematic Reviews and Meta-Analyses) flow diagram showing the number of articles identified throughout the search process.

We screened 867 article titles and abstracts and ultimately included 5 studies consisting of 3253 participants in the review (*Appendix C,*
Multimedia Appendix 1) [22-26]. There was a median of 6 attributes included in the 5 studies. Table 1 presents the key characteristics of each included study. The most important attribute among all studies was reducing the risk of dying from PC. In the studies that examined an opt-out option (3/5, 60%), which is a realistic choice, most men preferred not to have PC screening in 2 studies [23,26]. In the Charvin et al [23] study, which included an educational video about PSA-based screening, those randomized to the video significantly preferred no screening to getting screened. Howard and colleagues [25] also found that younger men valued preventing PC mortality more than older men, highlighting the need to integrate preference heterogeneity into future studies. Attributes that decreased the likelihood of getting screened for PC included higher risks of needing a biopsy and higher risks of adverse treatment effects. Finally, Pignone and colleagues [26] found that different value clarification methods produced different results on PSA screening decisions; that is, those who received a balance sheet are significantly more likely (*P*<.001) to choose PC screening (43.7%) than a rating and ranking method (34.2%) or DCE (20.2%). However, there was no statistically significant difference between the different methods (balance sheet, rating and ranking, and DCE) on *intention* to undergo PC screening. An important finding of the Pignone study is that when men were presented with unlabeled test options, they most often chose the no screening option. Whereas in the labeled item about whether they intended to get screened for PC, the men chose they intended to get screened. These studies collectively report that most men would prefer not to undergo PC screening given the risks of overdiagnosis and overtreatment. However, the studies also collectively suggest that men are willing to accept tradeoffs such as false positives and overdiagnosis if it means their PC is caught at an early stage.

The most common attributes studied in PC DCEs have been the reduction in PC mortality (N=5) as a result of getting screened, overdiagnosis and overtreatment (4/5, 80%) [22-25], and screening sensitivity (3/5, 60%) [22,25,26]. We adapted the checklist from the Hall et al [16] systematic review of cancer screening DCEs to guide the categorization of attributes (Multimedia Appendix 2). Three out of the 5 (60%) studies examined the adverse effects of PC treatment, which are treatment attributes and not screening attributes [22,25,26]. Only 1 (20%) study included attributes solely focused on PC screening. Crucially, there are no studies that included any attributes regarding the visit or provider that have been shown to be important in clinic visits with American Indian patients, highlighting an important literature gap [27,28]. Future work regarding PC screening in American Indian men needs to include culturally important attributes to ensure cultural responsiveness. Importantly, these studies were conducted in the mid-2010s and there have since been notable improvements in reducing the risks associated with biopsies and the use of magnetic resonance imaging to decide whether a biopsy is even needed [29].

**Table 1. T1:** Key characteristics from prostate cancer discrete choice experiments (total men studied, N=3253).

Study ID	Where conducted	Number of participants	Attributes	Key findings
Berchi and Launoy [22] (2019)	France	1008	Screening technique: PSA^a^ only; PSA with digital rectal examination (DRE)^b^ Mortality reduction: 10% and 20% Capacity to detect cancer: 50%, 70%, and 90% Risk of overdiagnosis due to screening: 20%, 40%, and 60% Risk of impotence due to treatment: 20%, 50%, and 80% Risk of incontinence due to treatment: 5%, 25%, and 40% Cost to the patient (€)^c^: 0, 15, and 30	The most important attribute in increasing the likelihood for prostate cancer screening was mortality reduction. Men had the greatest aversion to PSA only screening compared to DRE and PSA combination screening. Only 4.6% of men chose the no screening option.
Charvin et al [23] (2020)	France	854	Mortality by prostate cancer (per 1000): 2, 5, and 6 False positive result (per 1000): 50, 150, and 250 False negative result (per 1000): 1, 5, and 10 Overdiagnosis (per 1000): 10, 30, and 50 Recommended frequency: every year, every 2 years, and every 4 years Out of pocket costs (€): 0, 10, 20, and 40	Opting out of screening was the most common choice in this sample, chosen by 52.36% of men who watched the informative video. Watching the video increased the likelihood of opting out of prostate cancer screening. Increasing the risk of overdiagnosis increased the probability of choosing the screening option the most. The single most important attribute in the DCE^d^ was reducing prostate cancer mortality.
de Bekker-Grob et al [24] (2013)	The Netherlands	427	Risk reduction of death from PC: 10% relative risk reduction, 20% relative risk reduction, 30% relative risk reduction, and 50% relative risk reduction Screening interval: every year, every 2 years, and every 4 years Risk of unnecessary biopsy: 20%, 40%, 60%, and 80% Risk of unnecessary treatment: 0%, 20%, 50%, and 80% OOP costs (€): 0, 50, 100, and 300	The most important attribute in prostate cancer screening decision was reducing the risk of death from prostate cancer. The latent class model identified 3 latent classes, primarily due to education, willingness to pay for prostate cancer screening, and whether the respondent had anxiety or depression. Men are willing to trade off 2% risk reduction of prostate cancer-related death for 10% lower risk of overtreatment. Those in latent class 3 preferred not getting screened for prostate cancer, whereas those in latent classes 1 and 2 preferred screening compared to no screening.
Howard et al [25] (2015)	Australia and United States	662	Men who will die because of PC: 1, 3, 5/2, 5, 10/20, 30, and 40 Men diagnosed with PC (including overdiagnosed cancers in screened men): 5, 10, 15/100, 150, 200/500, 750, and 1000 Men who have unnecessary prostate biopsies from PSA test false alarms: 10, 20, 30/300, 400, 500/1500, 2000, and 2500 Men who experience ongoing impotence: 820, 835, 850/1350, 1375, 1400/4000, 4150, and 4300 Men who experience ongoing urinary incontinence or moderate/severe bowel problems: 305, 310, 320/580, 600, 650/750, 800, and 850 Approximate OOP cost to you over the next 10 years (AUD)^e^: 0, 1000, and 2500	Preference for avoiding prostate cancer-related death increased the likelihood of screening. Higher age was associated with lower preference for screening compared to no screening. Mortality reduction from prostate cancer was more important for younger men compared to older men. As number of biopsies, incontinence or bowel problems, and costs increased, preference was for no screening.
Pignone et al [26] (2013)	Australia and United States	302	Chance of being diagnosed with prostate cancer over 10 years (per 1000): 40, 60, 80 Chance of dying from prostate cancer over 10 years (per 1000): 2, 3, 4 Chance of having a prostate biopsy as a result of screening over 10 years (per 1000): 0, 240, 330 Chance of becoming impotent or incontinent as a result of screening over 10 years (per 1000): 0, 10, 20	79.8% of respondents in the DCE chose the unlabeled no screening option compared to the unlabeled PSA-style screening option. Intention to have PSA test among those in DCE was still high (73.5%), not statistically different from other survey methods. The most important attribute in the DCE was reducing the likelihood of death from prostate cancer.

a PSA: prostate specific antigen.

b DRE: digital rectal examination.

c The conversion rate in 2026, €1=US $1.17.

d DCE: discrete choice experiment.

e The conversion rate in 2026, Aus $1=US $0.72.

### Phase 2: Formative Qualitative Work to Inform Attribute Selection

#### In-Depth Interviews

Qualitative formative work is considered good practice when designing a DCE [20]. In general, the goal of qualitative research to inform DCE development is to elicit attributes and the potential attribute levels [30]. To better understand the knowledge, beliefs, and attitudes of Lumbee men toward PC screening and to inform the selection of attributes that are relevant to American Indian men, we will conduct in-depth interviews (IDIs). The interview guide (*Appendix D,*
Multimedia Appendix 1) based on the Health Belief Model elicits the American Indian men’s perspectives on PC susceptibility, perceptions of the seriousness of PC compared to other health risks, and perceptions on the effectiveness of getting screened for PC. We also used the Two-Eyed Seeing approach to identify culturally relevant aspects and Lumbee men’s attitudes toward sexual health conversations with health care providers and to better understand the context for PC screening decisions. Briefly, the Two-Eyed Seeing approach is an interweaving of indigenous knowledge and settler knowledge, acknowledging that both are important sources of knowledge and can improve health [31]. We will use the IDI findings to identify and prioritize attributes that are important to Lumbee men, with a particular focus on cultural responsiveness and incorporating Lumbee cultural norms.

#### Questionnaire

Participants will also complete a self-administered questionnaire to contextualize the findings from the IDIs. The questionnaire (*Appendix E,*
Multimedia Appendix 1) contains items from the HINTS (Health Information National Trends Survey) regarding perceptions of the likelihood of about getting PC and fatalism surrounding cancer diagnoses [29]. Participants will also complete the 1-item control preferences scale to determine role preferences in health care discussions [32]. Participants will then complete a series of items asking them about their preferences for types of health care providers in different scenarios (eg, primary care consultations and sexual health conversations). We will select the scenarios to identify whether there are any cultural norms or practices that would impact Lumbee men’s willingness to engage in conversations about their health and sexual health. Participants will also complete the Wake Forest University Trust in Doctors Short Form, the EuroQol 5D health-related quality of life (EQ-5D-5L), and sociodemographic items [33,34].

#### Participant Sampling and Recruitment

We will complete up to 15 in-person IDIs with Lumbee men in North Carolina. The interviewer is a trusted member of the Lumbee Tribe and a coauthor on this protocol (TL). According to Hollins’ guide, to conduct formative qualitative research for DCE attribute development, the emphasis is not on having a large sample size but to ensure representativeness in experience [30]. Thus, we will include American Indian men who have not been screened for PC, as well as men who have completed screening at least once, and those who have had PC. We obtained permission from the Lumbee Tribal Council prior to obtaining approval from our Institutional Review Board (IRB) and have partnered with the Lumbee Tribe and the local health system to help recruit participants for the IDIs. The IRB of the Wake Forest University School of Medicine is the primary IRB for our research.

#### Data Collection

The IDIs will be audio-recorded and transcribed into text to facilitate analysis. Interviews will be conducted virtually or in-person and audio-recorded.

#### Data Analysis

We will use a rapid reflexive thematic analysis using both inductive and deductive coding to analyze the qualitative data. The theoretical lens through which we will analyze the data includes using the Two-Eyed Seeing approach to ensure cultural responsiveness [31]. The team will use a codebook made of a priori structural codes based on the interview guide. The self-administered survey data will be analyzed using means and SDs for quantitative variables and percentages and frequencies for categorical variables. At the end of phase 2, we will have identified and prioritized key characteristics influencing PC screening among Lumbee men for inclusion in the DCE.

### Phase 3: DCE Development, Piloting, and Fielding

The DCE survey will involve respondents making iterative choices from sets of hypothetical scenarios that are characterized by preference-relevant features identified in phase 2. By systematically varying the attribute levels by means of an experimental design, participants must make tradeoffs between more- and less-preferred characteristics. The patterns of choices are then analyzed to quantify tradeoffs, as well as identify the relative importance of each feature, and predict the likelihood of PC screening uptake.

### Choice Context and Hypothesis

The study aims to identify the key considerations that American Indian men make when deciding about whether to get screened for PC. The choice context presented to the participants in the DCE will be framed as follows:

*Your doctor informs you that there is a blood-based test for PC, and that you are eligible for this test due to your age. Please consider the following scenarios. In which of these scenarios would you be more likely to test for PC?*

We hypothesize that American Indian men evaluate several screening attributes, such as mortality benefit, unnecessary biopsies, and treatment, as well as contextual factors, such as experiences with PC and the manner in which information is presented, when considering PC screening [25].

DCE choice tasks will resemble the task shown in Table 2. The sample task includes attribute levels identified in the literature review and several attribute levels hypothesized a priori to influence the choices of American Indian men; the selection of attributes and attribute levels in the actual DCE will be guided by the findings from phase 2. Columns represent screening options. Rows describe the attributes identified in phase 2. Cells represent feasible levels for each attribute. Each choice task involves the comparison of 2 hypothetical PC screening tests, followed by an “opt-out” question, that is, whether the participant would get tested in the preferred scenario, which reflects a realistic choice based on current USPSTF PC screening recommendations [10]. This opt-out option provides a reference point that allows for estimates of the potential uptake of PC screening. Prior to the choice tasks, participants will be introduced to each attribute, presented with *ceteris paribus* conditions (eg, the participant has insurance that covers the test), and will complete a training and comprehension task.

**Table 2. T2:** Example of discrete choice experiment choice task.

Attribute	Option A	Option B	Option C
Chance of identifying PC^a^ after it has spread	100 out of 1000 men like you would have PC diagnosed after it has spread	200 out of 1000 men like you would have PC diagnosed after it has spread	N/A^b^
Relative risk reduction of PC death from getting screened	Getting screened for PC would reduce the chance that you die because of PC by 25%	Getting screened for PC would reduce the chance that you die because of PC by 10%	Your chance of dying because of PC as a result of not getting screened is about 4%
Risk of false positive	4.6 men like you who get the test would have a biopsy from a false positive test result	2.3 men like you who get the test would have a biopsy from a false positive test result	N/A
Health care provider suggestion	Your doctor asks you whether you want to get screened	Your doctor suggests you get screened	Your doctor asks you whether you want to get screened
Which option do you prefer?	Option A	Option B	Option C

a PC: prostate cancer.

b Not applicable.

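### One stem tells all men aged 40 to 69 that age makes them eligible, while the guidance cited for the opt-out is given as 55 to 69, so a single pooled uptake would depend on the age mix recruited

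*Protocol article*

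**What the plan says.** The abstract's Methods paragraph states the DCE population as "100 Lumbee men between the ages of 40 and 69 years". This is the only place where the age range appears.

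Choice Context and Hypothesis prints one stem. In it a doctor mentions a blood-based test and tells the respondent "that you are eligible for this test due to your age". No variant by age is shown. The same section describes an opt-out question "which reflects a realistic choice based on current USPSTF PC screening recommendations" and gives its purpose: "This opt-out option provides a reference point that allows for estimates of the potential uptake of PC screening".

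The Introduction describes current USPSTF guidance as shared decision-making "starting at the age of 55 years through the age of 69 years". The only guidance it cites for younger ages is a baseline PSA test for Black men aged 40 to 45, presented as differing from USPSTF. It then says that "American Indian men are not identified by any organization as a high-risk population for PC".

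Primary and Secondary Outcomes makes screening uptake the main survey outcome and plans to rank strategies by expected uptake. DCE Data Analysis names the effects-coded attribute levels as the independent variables. Supplemental Survey collects age as a possible correlate of preferences.

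**The concern.** Three statements do not fit together: the age range, the eligibility sentence and the guidance cited for the opt-out. A man of 40 to 54 is told that his age makes him eligible, but nothing the article cites says so for an American Indian man of that age. The appeal to USPSTF recommendations covers the upper part of the age range only.

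This would be a matter of wording if age had no bearing on the answer. The article's own review suggests that it does. Table 1 reports, for the 2015 Australian and US study, that older men had a lower preference for screening relative to no screening. That is the contrast from which uptake is predicted. If the pattern holds here, one pooled figure depends on how many younger men respond to social media, emails, flyers and events. It would also tend to overstate uptake among men of 55 to 69, the group the cited guidance covers. A reader would have no way to tell which population the figure describes.

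**Working it through.** **The plan's own figure.** Sample Size and Statistical Power uses nta/c ≥ 500 with t = 10, a = 2, c = 4. Then n ≥ 500 × 4 / (10 × 2) = 100, as stated. At 25% response, 100 / 0.25 = 400 invitations, as stated. There is no dispute with these numbers.

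**The passages side by side.**

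| Item | Ages | Where |
|---|---|---|
| Men to be surveyed | 40 to 69 | Abstract, Methods |
| Men told they are eligible by age | all respondents, one stem | Choice Context and Hypothesis |
| USPSTF shared decision-making, cited for the opt-out | 55 to 69 | Introduction |
| Other guidance cited | 40 to 45, Black men | Introduction |

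The range 40 to 69 spans 69 − 40 + 1 = 30 single years of age, and 40 to 54 spans 54 − 40 + 1 = 15. So 15/30 = 50% of the age span lies below the ages given for the cited guidance. This is a share of the span, not of respondents; the documents do not give the age mix.

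**Effect on pooled uptake.** Let s be the share of respondents under 55, and U_y and U_o the uptake below 55 and at 55 to 69.

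U_pooled = s·U_y + (1 − s)·U_o, so U_pooled − U_o = s·(U_y − U_o).

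The documents give neither s nor the gap. Both are assumed below, in percentage points:

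| Share under 55 | Gap 10 | Gap 20 | Gap 30 |
|---|---|---|---|
| 30% | 3 | 6 | 9 |
| 50% | 5 | 10 | 15 |
| 70% | 7 | 14 | 21 |

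For scale, the 95% half-width of a simple proportion of 50% in 100 men is 1.96 × √(0.25/100) = 9.8 points.

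**What the sample allows by band.** With s from 30% to 70%, each band holds between 30 and 70 of the 100 men. The article's rule then gives 30 × 10 × 2 / 4 = 150 to 70 × 10 × 2 / 4 = 350 per band, and 250 at an even split. All are below 500. The corresponding half-widths for a simple proportion of 50% are 1.96 × √(0.25/30) = 17.9 points and 1.96 × √(0.25/70) = 11.7 points. These treat each man as giving one answer, so they indicate scale only; the model-based interval will differ.

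**The case against.** Several parts of the opposing case stand.

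- **The task is hypothetical.** The article calls the scenarios hypothetical and fixes other conditions for everyone, such as insurance cover. A reader might infer that younger men face an unreal decision. The documents do not support that: they call guidelines heterogeneous and do not say that men under 55 cannot be tested. The exact statement is that these men fall outside the guidance cited as justification.
- **Declining is realistic at any age.** The realism phrase attaches to the opt-out. A reader might infer that the opt-out is unrealistic below 55. If anything it is at least as realistic there. What lacks support is the eligibility sentence, and the appeal to USPSTF as the basis of the choice at those ages.
- **Preference results may be untouched.** DCE Data Analysis names preference weights as the primary outcome of this phase. If age shifts only the screening constant, then the weights, the marginal rates of substitution and probably the ranking of strategies do not change. The literature review does note that "younger men valued preventing PC mortality more than older men", so weights could also vary by age, but that is a possibility and not shown for this population.
- **Silence is not proof.** A reader might infer that no age quota or age term is planned. A condensed article may leave both to a fuller plan, and age is collected. However, the independent variables that are named are attribute levels only, and the limitations say that the sample rules out investigating preference heterogeneity. A fuller plan would not cure the printed stem or its justification either.
- **The size has no source.** Neither the gap nor the age mix comes from the documents. This is correct.

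The limitation on heterogeneity does not dispose of the point. One prespecified term on one constant asks far less of the data than latent classes or separate models.

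**Conclusion.** The concern holds, limited to absolute predicted uptake. The age range, the eligibility sentence and the USPSTF justification must be reconciled. Which age range or screening rule is right is not judged here. A single pooled uptake would depend on the recruited age mix and would not represent men of 55 to 69, provided that uptake differs by age as Table 1 reports from a prior DCE.

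The size cannot be derived from the documents. The 3 to 21 points rest wholly on an assumed gap of 10 to 30 points and an assumed 30% to 70% of respondents under 55; with no gap the shift is zero. The point does not invalidate the attribute weights or trade-offs. It merits action because uptake is the main survey outcome and the Results section says that no DCE participant has yet been recruited.

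**What to change.** Before fielding:

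1. Use one common, neutral stem for all men that does not assert eligibility by age, for example *suppose your doctor offers you a blood test for prostate cancer*. Do not give different stems to different age bands: that would confound age with wording, and a difference in uptake could not be attributed to either. The planned cognitive interviews can test the new text.
2. Interact one prespecified age term (under 55 versus 55 and over, or continuous age) with the screening-versus-opt-out constant.
3. Report expected uptake by age band with intervals, labelled as descriptive.
4. Limit the statement that the choice "reflects a realistic choice based on current USPSTF PC screening recommendations" to men of 55 to 69, and say why the survey range is 40 to 69.

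The cost is a change of wording and one model term; age is already collected and the age range need not change. The downside is wider uptake intervals within each band. With about 30 to 70 men per band under the assumed mix, below the article's own cutoff, band results support description only and not separate preference models. A term on the constant alone will not detect attribute weights that vary by age, and the report should say so.
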